## Abstract

**Introduction:**

Despite the high number of operations and surgical advancement, rehabilitation after rotator cuff repair has not progressed for over 20 years. The traditional cautious approach might be contributing to suboptimal outcomes. Our aim is to assess whether individualised (early) patient-directed rehabilitation results in less shoulder pain and disability at 12 weeks after surgical repair of full-thickness tears of the rotator cuff compared with current standard (delayed) rehabilitation.

**Methods and analysis:**

The rehabilitation after rotator cuff repair (RaCeR 2) study is a pragmatic multicentre, open-label, randomised controlled trial with internal pilot phase. It has a parallel group design with 1:1 allocation ratio, full health economic evaluation and quintet recruitment intervention. Adults awaiting arthroscopic surgical repair of a full-thickness tear are eligible to participate. On completion of surgery, 638 participants will be randomised. The intervention (individualised early patient-directed rehabilitation) includes advice to the patient to remove their sling as soon as they feel able, gradually begin using their arm as they feel able and a specific exercise programme. Sling removal and movement is progressed by the patient over time according to agreed goals and within their own pain and tolerance. The comparator (standard rehabilitation) includes advice to the patient to wear the sling for at least 4 weeks and only to remove while eating, washing, dressing or performing specific exercises. Progression is according to specific timeframes rather than as the patient feels able. The primary outcome measure is the Shoulder Pain and Disability Index total score at 12-week postrandomisation. The trial timeline is 56 months in total, from September 2022.

**Trial registration number:**

ISRCTN11499185.

STRENGTHS AND LIMITATIONS OF THIS STUDYRaCeR 2 is a large randomised controlled trial investigating the clinical and cost-effectiveness of individualised (early) patient-directed rehabilitation after surgery to repair the torn rotator cuff of the shoulder.We will explore and address barriers to recruitment with the quintet recruitment intervention to optimise recruitment.In addition to self-reported outcome measures, participants will have an ultrasound scan at 12 months to assess rotator cuff repair integrity.The parallel health economic analysis will assess the cost-effectiveness of individualised (early) patient-directed rehabilitation in comparison to standard rehabilitation.

## Introduction

Shoulder pain associated with a rotator cuff tear can significantly affect a person’s quality of life.^1^ The number of operations to repair rotator cuff tears has increased over time.^2^ In 2018/2019, direct treatment costs in the UK National Health Service (NHS) amounted to £56.7 million.^3^ Following surgery, rehabilitation is provided to support patients’ recovery. Current standard rehabilitation in the UK NHS typically includes sling immobilisation for approximately 1 month. This has not changed for over 20 years and may be contributing to suboptimal outcomes.^4^

Our systematic review of 20 randomised controlled trials (RCTs) compared the effectiveness of early versus standard postoperative rehabilitation. We found no difference between the approaches for shoulder pain and disability up to 12 months, but early rehabilitation significantly improved range of movement.^5^ Rotator cuff re-tear after surgery is a concern for clinicians and underpins the rationale for more cautious approaches to postoperative rehabilitation. We found no difference in repair integrity between rehabilitation approaches, but rehabilitation protocols varied and approaches described as early mobilisation were more reflective of standard rehabilitation in the UK.^5^

In our RaCeR pilot, 73 patients from 5 NHS hospitals were randomised to individualised (early) patient-directed rehabilitation (EPDR) (advice to remove the shoulder sling as soon as able and move as symptoms allow) or standard rehabilitation (sling immobilisation for 4 weeks). Participants in the EPDR reported less shoulder pain and disability, returned to driving 18 days faster, had 4 fewer days lost from work over 12 weeks and fewer re-tears (30% vs 41%).^6^ These findings from our RaCeR pilot, combined with our favourable assessment of feasibility and an evaluation of the need for evidence using principles of value of information to research prioritisation, provided the basis for the fully powered RCT (RaCeR 2).

### Objectives

Our hypothesis is that individualised EPDR is superior to standard rehabilitation for shoulder pain and disability, measured using the Shoulder Pain and Disability Index (SPADI)^7^ at 12 weeks postrandomisation. The aim of RaCeR 2 is to assess the clinical and cost-effectiveness of individualised EPDR compared with NHS standard rehabilitation for pain and disability at 12 weeks after rotator cuff repair. The objectives include:

Understanding and mitigating barriers to recruitment.Shoulder pain and disability at 6 and 12 months, quality of life, time to return to drive and usual activities including work, further healthcare use, repair integrity and adverse events (AEs) to 12 months.Within-trial cost-consequence analysis from an NHS and personal social services perspective and model-based long-term cost-effectiveness analysis.

### Trial design

Pragmatic multicentre, open-label, RCT with internal pilot. It follows a parallel group design with 1:1 allocation ratio, with full economic evaluation and integrated quintet recruitment intervention (QRI).^8^

## Methods: participants, interventions and outcomes

This protocol paper follows the Standard Protocol Items: Recommendations for Interventional Trials.^9^

### Study setting

A minimum of 24 NHS orthopaedic and physiotherapy services across the UK will be opened for recruitment. The internal pilot will last 6 months (June–November 2023). The trial monitoring group (TMG) in consultation with the trial steering committee (TSC) will assess study progress and decide on progression based on the criteria in table 1.

**Table 1 T1:** Internal pilot progression criteria

Progression criteria	Red (stop)* <66%	Amber (amend)† ≥66%–99%	Green (go)‡ 100%
Average recruitment rate/site/month	<0.7	0.7–1.0	1.1
Sites open	<12	12–17	18
Participants recruited	<50	50–96	97

*Red: halt, do not progress to main study.

†Amber: review areas of weakness and make amendments accordingly.

‡Green: no action required, continue to main study.

### Eligibility criteria

#### Inclusion criteria

Adults (18 years or older) awaiting arthroscopic surgical repair of a full-thickness tear of their shoulder rotator cuff, of any size.Able to return to the recruiting centre or affiliated site for rehabilitation supported by physiotherapists trained to deliver the study interventions.

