### Sample size

The sample size calculation was based on total SPADI score at 12 weeks, powered to detect a minimal clinically important difference of 8 points between groups.^10^ Assuming an SD of 30 (the upper 80% confidence limit from our pilot study)^6^ at 90% power and significance level 5%, and using an independent t-test, results in 297 participants being needed per group (594 in total). However, using Analysis of Covariance (ANCOVA) (primary analysis), adjusting for the baseline SPADI score, where correlation (r) between baseline and 12 weeks=0.2 (data from pilot RaCeR RCT), the sample size was adjusted by (1-r2) plus one extra participant per group to 574 in total.^11^ In addition, adjusting for 10% non-response of SPADI questionnaire at 12 weeks, a target of 319 participants should be randomised per group, 638 in total.

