### Data collection, management and analysis

#### Plans for assessment and collection of outcomes

Following consent, the baseline questionnaire will be completed prior to surgery in-person or remotely. Completion of the baseline questionnaire will require input from local site staff and participants. The questionnaire will include the SPADI and EQ-5D-5L validated questionnaires and demographic data. The SPADI has 13 items divided into 2 subscales: pain (5 items) and disability (8 items). The responses are indicated on a Visual Analogue Scale (0=no pain/no difficulty and 10=worst imaginable pain/so difficult it requires help). The items are summed and converted to a total score out of 100, a high score indicates greater pain and disability.^7^ The EQ-5D-5L is a generic measure of health-related quality of life. It provides a single index value for health status that can be used in a clinical or health economic evaluation.^14^ The EQ-5D-5L consists of questions relating to five health domains (mobility, self-care, usual activities, pain/discomfort and anxiety/depression) and respondents rate their degree of impairment using five response levels (no problems, slight, moderate, severe or extreme problems). The EQ-5D-5L is the National Institute for Health and Care Excellence’s preferred measure of health-related quality of life in adults.

Follow-up questionnaires, including SPADI, EQ-5D-5L, self-report questionnaire for healthcare resource use, time to return to usual activities (including work) and any AEs, will be completed at 12 weeks, 6 and 12 months after randomisation (+4 weeks visit window to allow for reminders). This process will be coordinated centrally by the DCTSU. Follow-up questionnaires will be available in paper or electronic format. At 12 months following surgery, participants will be asked to undergo an ultrasound scan.

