#### Definition of analysis population relating to protocol non-adherence and any statistical method to handle missing data

Per-protocol analysis will consider patients with time out of the sling of 222.6 hours or more over 4 weeks compared with those with time out of the sling less than 222.6 hours base on the cut-off values from the RaCeR pilot.^6^ Missing values in the diary will not be included in the analysis.

Complete-cases analysis will be undertaken as part of the primary endpoint analyses, where cases with missing values or those completed outside the 4 weeks window will be excluded in each analysis. If substantial missing data (>10% and <20%) are observed in SPADI at 12 weeks or a key prognostic covariate for the primary analysis, then multiple imputation using chained equations will be applied. Complete-cases analysis will be undertaken for the secondary study outcomes.

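### A missing pre-operative SPADI removes a randomised participant from the primary ANCOVA even when the 12-week score is observed, and the sample size does not allow for this

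*Protocol article*

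**What the plan says.** All references are to the protocol article.

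- **Entry.** The first item under Inclusion criteria admits "Adults (18 years or older) awaiting arthroscopic surgical repair of a full-thickness tear of their shoulder rotator cuff, of any size". The other inclusion and exclusion items concern attendance for rehabilitation, the findings at surgery, consent and co-enrolment. None mentions the baseline questionnaire, and neither do the sections on sequence generation, concealment and implementation.
- **Timing.** Under Plans for assessment and collection of outcomes: "Following consent, the baseline questionnaire will be completed prior to surgery in-person or remotely". The same section says that site staff as well as participants contribute to completing it. Under Sequence generation, randomisation takes place when surgery is complete.
- **Primary model.** Primary and secondary outcome analysis specifies an intention-to-treat ANCOVA of the 12-week total SPADI, with baseline SPADI as the only named covariate.
- **Missing data.** In the primary endpoint analyses, "cases with missing values or those completed outside the 4 weeks window will be excluded in each analysis". Multiple imputation by chained equations applies if more than 10% and less than 20% is missing in the 12-week SPADI or in a key prognostic covariate.
- **Allowance.** Sample size states: "adjusting for 10% non-response of SPADI questionnaire at 12 weeks, a target of 319 participants should be randomised per group, 638 in total".

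**The concern.** The exclusion rule treats a missing baseline in the same way as a missing outcome, but the two differ. A participant without a 12-week SPADI has no outcome to analyse. A participant without a baseline SPADI may have the outcome in full and lack only a covariate used to gain precision.

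Dropping that person discards an observed primary outcome and takes a randomised participant out of an analysis described as intention-to-treat. It cannot be repaired afterwards: the reminder and telephone steps under the retention plan concern questionnaires not completed at the expected timepoints, and nothing collected after the operation is a pre-operative score. Remote consent and remote completion are allowed, including for patients who do not return to the site before surgery, so an occasional unreturned form is foreseeable. At stake are some power, for which the target has no margin, and the integrity of the stated analysis set.

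**Working it through.** **Inputs (Sample size section).** Difference: "powered to detect a minimal clinically important difference of 8 points between groups". SD 30; power 90%; significance level 5% (taken as two-sided, since sidedness is not stated); baseline to 12-week correlation r = 0.2; 12-week non-response 10%; allocation 1:1.

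**Step 1: reproduce the plan's figure.**
- The t-test with difference 8 and SD 30 gives 296.5 per group, rounded up to 297 (594 in total).
- ANCOVA: 297 × (1 − 0.2²) = 285.12, rounded up to 286; plus 1 = 287 per group, 574 in total.
- Non-response: 287 / 0.9 = 318.9, rounded up to 319 per group, 638 in total.

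All three stated figures are reproduced.

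**Step 2: look for a margin.** 638 × 0.9 = 574.2, against 574 required. The 10% is fully used by 12-week non-response.

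**Step 3: add missing baselines.** The document gives no rate, so m is an assumed share without a baseline SPADI, taken as independent of 12-week non-response.
- Analysed number N = 638 × 0.9 × (1 − m). Each 1% costs 574.2 × 0.01 = 5.7 participants.
- Residual SD = 30 × √(1 − 0.04) = 29.39.
- Noncentrality = (8 / 29.39) × √(N / 4). Power is from the noncentral t distribution, two-sided 5%.
- The last column is the number to randomise so as to keep 287 complete cases per group: 2 × 287 / (0.9 × (1 − m)), rounded up per group.

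| m (assumed) | N analysed | Power | Number to randomise |
|---|---|---|---|
| 0% | 574 | 90.2% | 638 |
| 2% | 563 | 89.7% | 652 |
| 5% | 545 | 88.7% | 672 |
| 10% | 517 | 87.0% | 710 |

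A normal approximation agrees within 0.2 percentage points (90.3% at m = 0, 87.2% at m = 10%).

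**Step 4: does the imputation clause cover these cases?** Baseline SPADI is the only covariate named for the primary ANCOVA, so it plausibly counts as a key prognostic covariate. Every row of the table has m at or below 10%, so the baseline itself does not trigger imputation and exclusion applies. The clause may also be triggered by 12-week missingness between 10% and 20%, but the text does not say whether a missing baseline would then be filled as well.

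**Step 5: what keeping these participants recovers.** Those with a filled-in baseline contribute variance 30² = 900, and the rest 900 × 0.96 = 864. The average is 864 + 36m. At m = 10% this is 867.6, an SD of 29.46; with N = 574.2 the noncentrality is (8 / 29.46) × √143.55 = 3.25, and power is about 90.1% rather than 87.0%.

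**The case against.** The strongest reply is that the article contains no false statement here. The inclusion criterion is correct as written. The baseline form is scheduled before surgery with staff input, so a participant randomised without it departs from the described procedure. A reader might infer that a completed baseline SPADI is not required for randomisation. The document does not support that: it shows only that the article states no such check. The article condenses a full protocol that is not shown, its flow diagram and assessment schedule are not visible, and a required field in the online system would normally be described elsewhere. This part of the objection stands, so the point is not about eligibility.

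A reader might also infer that such participants can never enter the primary analysis. That is too strong as well, because imputation is provided for between 10% and 20% missing.

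Three further replies bear on size, and all stand:
- The rates are assumed, and if people who miss the baseline form also miss week 12, the losses overlap and the added cost is smaller.
- SD 30 is an upper 80% confidence limit from the pilot, so true power may be higher throughout.
- The missingness arises before allocation and cannot depend on arm, so no arm-related bias is expected from it.

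A strict entry requirement would also cost a pragmatic trial some patients who could still contribute to outcomes such as re-tear, return to work and driving, and adverse events.

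None of this removes the printed exclusion rule, its mismatch with the intention-to-treat label at 10% missing or less, or the restriction of the allowance to 12-week non-response.

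**Conclusion.** The point holds as one about the missing-data rule. As written, a randomised participant with an observed 12-week SPADI and no baseline SPADI is excluded from the primary ANCOVA unless the imputation trigger is met, and the target of 638 has no room for such losses. The effect is modest: at an assumed 2% to 10% missing, power falls by about 0.5 to 3.2 percentage points from 90.2%. The figures rest on the plan's own difference, SD and correlation, a two-sided 5% test, exactly 10% non-response at 12 weeks, and independence between the two kinds of missingness. The departure from intention-to-treat does not depend on the rate. A small change removes both problems, so it should be made.

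**What to change.** Amend the missing-data paragraph so that participants with an observed 12-week SPADI and a missing baseline SPADI stay in the primary ANCOVA whatever the missing rate. Replace the missing baseline with the overall baseline mean, pooled across arms, and add a missing indicator to the model. Because the covariate precedes randomisation and the fill-in ignores allocation, this does not favour either arm.

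In addition, confirm that the randomisation system checks that the pre-operative SPADI has been received, with site staff collecting it before surgery if it has not. This is a safeguard and not a correction of the eligibility criteria; if the full protocol or the system already does it, nothing needs to change.

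The cost is a negligible amount of extra analysis work. The sample size, outcome and treatment comparison are unchanged.

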#### Exclusion criteria

Do not have a full-thickness tear at surgery and/or arthroscopic repair is not undertaken.Unable to provide informed consent.Taking part in another research study that mandates a specific postoperative rehabilitation pathway.

### Recruitment and informed consent

Patients listed for rotator cuff repair surgery are screened and assessed for eligibility by trained local hospital site staff. Once an eligible patient has been identified and has been allocated a date for surgery, they are provided with an information pack about the study (including the optional QRI; more details below) and consent forms. Patients will be given the opportunity to discuss RaCeR 2 with support from an interpreter as required. We provide translated information sheets in Arabic, Bengali, Korean, Nepali, Polish, Punjabi, Turkish, Urdu and Welsh; potential recruiting sites identified these languages as the most common languages spoken other than English in their areas. Recruiters will follow up with the patient to discuss the study and answer any questions. Patients may consent to participate in neither, either or both the QRI and RaCeR 2 trial. Separate QRI clauses relating to recording of discussions about the study are included within the consent form. The process of gaining informed consent may be wholly or partly undertaken remotely or in-person depending on local site and patient circumstances. If it is not possible to get written consent, for example, if the patient is not returning to the recruiting site prior to surgery, verbal remote consent will be acceptable to avoid unnecessary burden for the patients and site staff. The consent form is completed by the recruiter indicating that consent was taken verbally and a copy provided to the participant. This is the same for patients who consent to the audio recording of their discussion (QRI) but not to participating in RaCeR 2. Consent is fully documented within the patient’s medical notes, including the method of consent (remote/in-person and written/verbal). Figure 1 shows the study flow diagram.

**Figure 1 F1:**
[figure not shown]
Study flow diagram. DCTSU, Derby Clinical Trials Support Unit; NHS, National Health Service.

### Interventions

#### Individualised EPDR

EPDR is an individualised approach where shoulder movement, sling removal and exercise are progressed as the participant feels able within the context of their own pain experience and tolerance. Individualised EPDR includes advice to the patient from a physiotherapist within 24 hours following surgery to remove their sling and gradually begin to actively use their arm as they feel able and within acceptable limits of pain. The advice to remove the sling is complemented by an exercise programme supervised by a physiotherapist and practised at home. After the first session with the physiotherapist, participants access follow-up with a physiotherapist according to usual care agreements. Follow-up sessions can be either face to face or remote.

#### Standard (delayed) rehabilitation

Standard (delayed) rehabilitation includes advice to the patient from a physiotherapist within 24 hours following surgery to wear their sling for 4 weeks except for when eating, washing, dressing or undertaking the exercises prescribed. After the first session with the physiotherapist, participants access follow-up with a physiotherapist. The exercise programmes will be staged as follows^6^:

Stage 1: Fully assisted (passive) shoulder movement.

Stage 2: Partially assisted (active assisted) with progression to full non-assisted (active) shoulder movement.

Stage 3: Resisted static exercises (isometric).

Stage 4: Resisted exercises through shoulder range of movement (dynamic) within limits of pain progressing to functional restoration.

#### Difference between current and planned care pathways

Participants in both groups agree to the number of rehabilitation sessions with their physiotherapists; there is no prespecified number of sessions. It is expected that approximately five follow-up appointments will be scheduled over the 12-week period following surgery. This means that both treatments are delivered within the parameters of current NHS physiotherapy provision. The key difference between the two rehabilitation approaches is that the individualised EPDR promotes an approach to rehabilitation which reflects patient factors including pain, preoperative levels of function and psychological well-being. It aims to promote self-efficacy whereby the patients feel they have increased control over their recovery. Both groups will start with stage one of the specific exercise programme but the intervention group will be supported to progress through the stages as they feel able. The control group will remain at stage 1 for a minimum of 4 weeks. Patients undergoing individualised EPDR are invited to resume activities in line with their individual progress rather than preset timescales. Patients receiving standard rehabilitation will progress through stages based on specific time frames after surgery; stage 1 (0–4 weeks), stage 2 (4–6 weeks), stage 3 (6–8 weeks) and stage 4 (8–12 weeks). Surgeons and physiotherapists will treat patients in both arms of the trial and multiple clinicians will be involved in patients’ treatment in each arm.

